#### Randomisation of patients in the trial

Once written informed consent has been obtained to participate in the trial, and baseline data collected, patients will be randomly allocated (1:1 allocation ratio) to either the intervention or the wait-list arm of the trial. Site coordinators will contact a randomisation line at Lancaster University, and the next sequence in the allocation (stored in sequentially numbered sealed opaque envelopes) will be revealed. The randomisation sequence will be computer generated by an experienced statistician outside the study context, with rebalance in the arms after 10 randomisations. Blinding of site staff and patient participants will not be possible due to the nature of the intervention.

## Data collection methods

### Outcome measures

The causal impact of the intervention on each aspect of end of life experience examined in this study will be measured using a pre-determined set of outcome measurement tools as follows:Quality of life (primary outcome measure) is measured using the World Health Organisation Quality of Life (WHOQOL-BREF) Scale, a short validated measure of quality of life and wellbeing, having wide breadth. Our primary outcome will be overall quality of life (single response question), with secondary outcomes the quality of life domains measured by the WHOQO-BREF (social, environmental, psychological and physical domains) [21].Loneliness (secondary outcome measure) is measured using the De John Greiveld 6-item Loneliness Scale, a short, well-used, reliable and valid measurement instrument for overall, emotional, and social loneliness, chosen for brevity and relevance of the items when mapped onto anticipated outcomes [22].Social Support (secondary outcome measure) is measured using the 8-item modified Medical Outcomes Study Social Support Survey (mMOS-SS), a short validated scale covering two domains (emotional and instrumental social support) designed to identify potentially modifiable social support deficits, chosen for brevity and relevance of the items when mapped onto anticipated outcomes [23].Carer Burden (secondary outcome measure) is measured using the Caregiver Burden Scale-End of Life Care (CBS-EOLC), a reliable and valid measurement tool designed to specifically assess family caregivers’ burden within the palliative care context, chosen for brevity and relevance of the items when mapped onto anticipated outcomes [24].

Socio-demographic data (age, gender, disease diagnosis, education, marital status, living status, spirituality and ethnicity) in the form of a self-completed questionnaire will be collected from both patients and informal carers at baseline. At baseline and subsequent time points patient participants will also be asked to indicate the number, type and frequency of contact they have with networks of others (to include social networks and contact with health and social care service providers). After baseline, week 4, 8 (and 12) questionnaires (with paid return envelope) will be mailed to participants by research staff at Lancaster University, with reminders after 2 weeks if required.

### Participant timeline

#### Patient questionnaires

Baseline data (including socio-demographic data such as age, gender, disease diagnosis, education, marital status, living status, spirituality and ethnicity) will be collected from both patients and carers prior to randomisation. The patients randomised to immediately receive the service will do so (following any service administrative procedures) and continue to receive it for as long as required as assessed by the service providers in conjunction with service recipients. At week 4 all participants (intervention arm and wait-list arm) will complete the outcome measures. At this point, the patients on the wait-list arm will also commence receiving the service. Measures will be repeated at week 8. those on the wait-list arm will complete an additional questionnaire at week 12. Participants who withdraw from the service will not be required to complete questionnaires as this may be due to deterioration in physical condition, and the risk of sending questionnaires inappropriately if the services are unable to provide updates on their health status.

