**Methods/design:**

The research questions will be addressed through a wait-list randomised controlled trial (WLRCT) and qualitative case study evaluation across 12 sites in England. Participants will be randomly allocated to either receive the social action volunteer befriending service straight away or receive the intervention after a four week wait (wait-list arm). The impact of the intervention on end-of-life experience (quality of life as primary outcome, loneliness, social support) will be measured. Repeated assessments will be carried out at baseline and weeks 4 and 8 for the intervention arm and weeks 4, 8 and 12 for the wait-list arm. For selected sites case study evaluation will include interviews, observation and documentary analysis to understand the mechanisms underpinning any found impact.

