#### Wait-list randomised controlled trial

This is a multi-site (*n* = 12) randomised controlled trial (RCT) involving a wait-list design. Participants will be allocated on a 1:1 allocation ratio. A wait-list trial was chosen as an ethical design which has the strength of an RCT, but with greater acceptability as all patients eventually receive the intervention. In a wait-list trial, respondents are either allocated to an intervention group where they receive the intervention immediately (or as soon after randomisation as possible) or to a wait-list group where they receive the same intervention after a defined period on a waiting list. While they are on the waiting list patients receive standard/usual care. Wait-list designs have been successfully used in end-of-life care research, including where there is a pre-existing service [13, 14]. Advantages include having the strength of a RCT in determining causality, but with greater acceptability as all patients eventually receive the intervention which can feel more ethically defensible in end of life care [13–18]. We propose a short wait period to minimise risk and acknowledge that interventions need to be effective in a short time period where life expectancy is short (i.e. a year or less) and attrition due to illness or death highly anticipated [19].

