### Additional data

Each participating site will collect information about volunteer visits and record per patient participant details such as: referral date, consent date, allocation arm, dates of assessments date allocated to a volunteer, first date of volunteer visit, dates/numbers of volunteer visits and brief indication of support given and dates/numbers of volunteer support through calls/texts or skype.

A schedule of enrolment, interventions and assessment of outcomes is provided in Table 1.

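### Nothing stated ensures that wait-list participants complete the postal week-4 questionnaire before their first volunteer contact, so the only comparison with usual care alone may include exposed control replies

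*Protocol article*

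**What the plan says.** Protocol article, Participant timeline, Patient questionnaires: "At week 4 all participants (intervention arm and wait-list arm) will complete the outcome measures. At this point, the patients on the wait-list arm will" begin the service. The measurement and the end of the control condition are thus set at the same nominal point.

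Protocol article, Outcome measures: the "week 4, 8 (and 12) questionnaires (with paid return envelope) will be mailed to participants by research staff" at the university, "with reminders after 2 weeks if required". No posting day and no latest acceptable return date are given.

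Protocol article, Wait-list randomised controlled trial, defines the control condition: "While they are on the waiting list patients receive standard/usual care".

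Protocol article, Additional data: sites record, for each patient, the "first date of volunteer visit, dates/numbers of volunteer visits", together with assessment dates and the date of allocation to a volunteer. The article links none of these dates to the outcome analysis.

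**The concern.** The primary aim compares the service plus standard care with usual care alone. By week 8 both arms have the service, and week 12 is measured only in the wait-list arm. Week 4 is therefore the one follow-up that can answer the primary aim, and the analysis section itself speaks of a treatment effect at 4 weeks.

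A form posted around week 4 and reminded two weeks later can be completed when a wait-list patient already has a volunteer. That reply would be analysed as usual care although the patient is exposed. If the service works quickly, such replies pull the control mean towards the intervention mean. The model in Comparison between arms has terms for site, treatment group, time since entry and time interactions. Even if time since entry means actual days, none of the listed terms marks when a wait-list patient became exposed.

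**Working it through.** **1. Timetable.** Nominal week 4: form due and wait-list service starts (Patient questionnaires). Two weeks after posting: reminder (Outcome measures). If posting is at week 4, which is an assumption, the reminder falls at week 6, half way to the week-8 assessment. The intervention section gives 1–3 contacts a week, so with a prompt start a wait-list patient could have had 2 × 1 = 2 to 2 × 3 = 6 contacts by then.

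**2. The plan's own power.** Inputs from Trial power calculation and sample size: 350 per arm, 5% attrition, f = .10, two-sided alpha .05, r = .6 at 4 weeks.
- Analysed per arm: 350 × 0.95 = 332.5.
- Two groups: d = 2f = 0.20.
- SD of the baseline-to-week-4 change: √(2 × (1 − 0.6)) = √0.8 = 0.894.
- Standard error: 0.894 × √(2/332.5) = 0.0694, and 0.20/0.0694 = 2.88.
- Power: Φ(2.88 − 1.96) = 0.82. This agrees with the stated power above .80. ANCOVA, with SD √(1 − 0.36) = 0.80, gives 0.90.

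**3. Late replies in both arms.** Both arms get the same mailing and reminder, so a late reply also means longer exposure in the immediate arm. Let B(t) be the benefit after t weeks from the planned start, q the share of late replies in each arm, and late mean week 6. The immediate arm is then at 6 weeks and the wait-list arm at 2 weeks. Relative to an on-time contrast of B(4):

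d observed = 0.20 × [1 − q + q × (B(6) − B(2)) / B(4)]

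*Linear accrual, no start lag:* (6 − 2)/4 = 1, so d stays 0.20 and power stays 0.82. There is no loss.

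*Saturating accrual:* B(t) = 1 − exp(−(t − L)/τ), with τ the time constant in weeks and L a start lag in weeks common to both arms. The values of τ, L and q are assumptions; the documents give none of them.

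| τ | L | (B(6) − B(2))/B(4) | d, q = 20% / 40% | Change-score power, q = 20% / 40% |
|---|---|---|---|---|
| 4 | 1 | 0.93 | 0.197 / 0.195 | 0.81 / 0.80 |
| 4 | 0 | 0.61 | 0.184 / 0.169 | 0.76 / 0.68 |
| 2 | 1 | 0.68 | 0.187 / 0.174 | 0.77 / 0.71 |
| 2 | 0 | 0.37 | 0.175 / 0.149 | 0.71 / 0.58 |
| 1 | 1 | 0.38 | 0.175 / 0.150 | 0.71 / 0.58 |
| 1 | 0 | 0.14 | 0.165 / 0.131 | 0.66 / 0.47 |

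Example, last row, q = 40%: B(2) = 0.865, B(4) = 0.982, B(6) = 0.998. The ratio is (0.998 − 0.865)/0.982 = 0.14, so d = 0.20 × (0.6 + 0.4 × 0.135) = 0.131.

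**4. Margin.** The change-score margin over .80 is thin: a 5% dilution (d = 0.19) already gives 0.78.

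**The case against.** The strongest case against is that the overlap is inferred. No posting day is stated, and completion at week 4 is consistent with posting a few days ahead. Mailing dates and return windows are details that an article may leave to the full protocol. This stands as a limit on certainty. It does not remove the point, because the two sections as written allow the overlap and give no order for the questionnaire and the first contact.

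A reader might infer several stronger things that the documents do not support:

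- *That many wait-list replies are contaminated, or that every reminded reply is.* No return times or reminder rates are given. The intervention section has a co-ordinator assess needs before support is provided, and Additional data records allocation to a volunteer separately from the first visit. The first contact may therefore come well after week 4. The allowance for administrative procedures is written only for the immediate arm, but these steps are not tied to an arm.
- *That power drops to 0.74–0.64, or even to 0.64–0.41.* Those figures come from 0.20 × (1 − q × k), with q = 20–40% late and k = 0.5 or 1 of the benefit already reached. They give late controls extra exposure but hold late immediate-arm replies at 4 weeks. With k = 0.5, which is linear accrual after 2 of 4 weeks, the whole loss disappears once both arms move.
- *That the analysis uses nominal weeks only, or that no dates exist.* Time since entry could be actual time. The assessment dates that sites record may cover some completions, although that wording is ambiguous and the forms go by post to the university.
- *That the damage can never be examined afterwards.* With completion dates and first-visit dates, the overlap can be counted. An exposed reply still cannot be turned into an unexposed one.

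**Conclusion.** The point holds as a gap in the stated schedule. The two sections put the postal week-4 assessment and the wait-list service start together, with a two-week reminder, and nothing shown secures completion before the first volunteer contact. Any bias is towards no difference, and it arises if benefit comes early.

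Its size cannot be fixed from the documents. It is nil under linear accrual with equal lateness in both arms. With 20–40% late replies, time constants of 1–4 weeks and a start lag of 0–1 week, all assumed, change-score power runs from about 0.81 down to about 0.47, against 0.82 without late replies. The low end needs fast benefit, a prompt start and 40% late replies together. The protocol does argue that interventions in this population must work within a short time, so early benefit is not a remote case. The change is worth making because it is cheap and must come before data collection.

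**What to change.** - Reconcile the Outcome measures and Patient questionnaires sections on the order of questionnaire and service start. The service start itself is not to be changed.
- In both arms, post the week-4 questionnaire some days before week 4, so that it can be returned before the wait-list service starts, and use a shorter reminder interval for this assessment.
- Put a completion date on each form.
- Report how many wait-list week-4 replies post-date the recorded first volunteer contact.
- Keep the intention-to-treat analysis of all replies as primary. Prespecify a sensitivity analysis restricted to week-4 replies completed by a fixed day, applied identically in both arms.

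Cost: a changed mailing date, one date field and one extra analysis. The immediate arm has a few days less exposure when measured. The sensitivity analysis is a post-randomisation restriction, since late responders may be sicker and lateness may differ by arm, so it can support the primary result but not replace it.

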### Comparison between arms

Data will be analysed on an intention to treat basis. A linear mixed effect model (LME) will be fitted to each outcome variable at 4, 8 and 12 weeks. The random effects are intercept and slope; which posit that each participant has a “personalized” linear response to treatment. The fixed effects include site, treatment group, and time since entry, and time interactions, which measure systematic differences in the rate of change. The assumption of a common initial mean for all participants is justified by the randomization of participants into treatment groups. A major advantage of the LME model is that is does not require a balanced design; in particular, participant effects can be estimated using incomplete data. However, missing-completely-at-random (MCAR) assumption will be tested, and in case that this assumption is not tenable, multiple imputation procedures will be employed.

Analyses will be conducted to evaluate potential variables associated with dropout in wait-list controls, to prevent that this attrition inflates the apparent treatment effect at 4 weeks by comparing the intervention group with only those in the wait-list group with some particular features. If observed, these confounders will be included in the LME model to reduce the bias of differential attrition on the estimated treatment effect.

Statistical significance will be assessed at the 5 % (two-sided) level. All statistical analyses will be conducted using SPSS v.20.

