### Missing data

A complete case analysis will be undertaken with a range of approaches for undertaking sensitivity analyses to access the robustness of the findings with respect to missing data.

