Finally, the risk that participants will be contacted to complete subsequent questionnaires or to be invited to interview when they may be too unwell through deterioration in their condition, or that carers may be distressed by such information after a participants’ death will be mitigated by a clear protocol between the sites and the University to ensure that this information is securely transferred to avoid such distress.

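### Ending questionnaires on withdrawal from the service makes week-4 follow-up depend on service use, mainly in the immediate arm, and can bias the intention-to-treat comparison

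*Protocol article*

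**What the plan says.** The Patient questionnaires section of the protocol article sets the follow-up rule: "Participants who withdraw from the service will not be required to complete questionnaires as this may be due to deterioration in physical condition". The sentence goes on to give a second reason: a questionnaire might be sent inappropriately when the service cannot say how the person is.

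The same section says "At week 4 all participants (intervention arm and wait-list arm) will complete the outcome measures", and of the wait-list arm, "At this point, the patients on the wait-list arm will also commence receiving the service".

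Under Comparison between arms the principle is "Data will be analysed on an intention to treat basis". That section plans a mixed model on incomplete data, a test of missing completely at random, and "in case that this assumption is not tenable, multiple imputation procedures will be employed". It also plans a dropout analysis: "Analyses will be conducted to evaluate potential variables associated with dropout in wait-list controls". The Missing data section adds: "A complete case analysis will be undertaken with a range of approaches for undertaking sensitivity analyses".

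The Risks section says that the danger of contacting people who are too unwell, or carers after a death, "will be mitigated by a clear protocol between the sites and the University".

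**The concern.** Whether a week-4 outcome is sought depends on something that happens after randomisation: staying in the service. Week 4 is the only follow-up at which the wait-list arm has not yet had the service, so it carries the clean randomised comparison. Up to that point mainly the immediate arm has a service to leave.

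The article itself links leaving to physical decline. If that link holds, declining patients are removed from one arm by rule, while similar patients in the other arm are still sent the questionnaire unless the site reports them too unwell. The planned effect is small (f = 0.10), so a modest selection effect could account for a sizeable part of it.

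The article recognises that attrition can inflate the apparent effect at 4 weeks, but it looks for the cause only among wait-list controls. Scores that were never sought cannot be recovered by any later analysis plan.

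**Working it through.** **1. The plan's own figure.** From the Trial power calculation section: 350 per arm, 5% attrition, f = 0.10, two-sided alpha 0.05, r = 0.6 at 4 weeks.
- Target difference for two groups: d = 2f = 0.20 SD.
- Analysed per arm: 350 × 0.95 = 332.5.
- Variance of a change score in units of the outcome SD: 2(1 − 0.6) = 0.8, so SD = 0.894.
- Standard error of the difference: sqrt(2 × 0.8 / 332.5) = 0.0694.
- Power: 0.822. The stated power above 0.80 is reproduced.

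**2. Who can lose a week-4 score through the rule.**
- Immediate arm: receiving the service from soon after randomisation, so can withdraw from it before week 4.
- Wait-list arm: not receiving it until the week-4 measure. The article does not say whether leaving the waiting list counts as withdrawing from the service.
- Hence the loss falls mainly, though not provably only, on the immediate arm.

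**3. Size of the bias if withdrawers do worse.** The article gives neither input, so both are assumptions: p is the share of the immediate arm withdrawing before week 4, and g is how far below the whole-arm mean the withdrawers would have been, in SD. The observed arm mean is then too high by p × g / (1 − p). With no true effect, the two-sided error is Φ(b/SE − 1.96) + Φ(−b/SE − 1.96), with SE = 0.0694.

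| p | g | Bias b (SD) | Share of 0.20 | Two-sided error |
|---|---|---|---|---|
| 5% | 0.5 | 0.025/0.95 = 0.026 | 13% | 6.7% |
| 5% | 0.8 | 0.040/0.95 = 0.042 | 21% | 9.3% |
| 10% | 0.5 | 0.050/0.90 = 0.056 | 28% | 12.6% |
| 10% | 0.8 | 0.080/0.90 = 0.089 | 44% | 24.9% |
| 20% | 0.5 | 0.100/0.80 = 0.125 | 63% | 43.7% |
| 20% | 0.8 | 0.160/0.80 = 0.200 | 100% | 82.2% |

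Removing the withdrawers from the immediate arm's sample size as well raises the SE at p = 10% to 0.0713 and changes the error rates to 12.2% and 23.9%, so the simplification is minor.

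**4. Does baseline adjustment remove it, and is the direction fixed?** A simulation under no true effect used 350 per arm, 5% random loss in both arms, further withdrawal in the immediate arm only, a baseline-adjusted week-4 analysis and 2,000 replicates.
- Withdrawal correlated 0.5 with decline: bias +0.04, +0.07 and +0.13 SD at 5%, 10% and 20% withdrawal, with error rates of 9%, 20% and 51%.
- Withdrawal unrelated to change: bias about 0.
- Withdrawal linked to improvement (correlation 0.3): bias −0.02 to −0.075 SD, against the intervention.
- Same loss process in both arms (10% and 20%, correlation 0.5 with decline): bias about 0, error 4% to 5%.

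A patient who leaves before week 4 has a baseline score only. A mixed model, or imputation from baseline data, has no sight of decline after baseline, so it leaves the bias in the first case.

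**The case against.** The strongest defence is that the rule protects very ill people, and that its second reason is practical: once someone leaves, the site may no longer know how they are. The safeguard in the Risks section depends on sites having that knowledge. A reader might infer that this safeguard already makes the rule unnecessary. The article does not support that, because status may be missing for exactly these people. This part of the objection stands and shapes the fix.

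Three other strong readings are tempting.
- *Poor outcomes are deleted in one arm only.* The Risks safeguard covers participants in both arms, wait-list patients may also leave early, and a mailed questionnaire is not always returned. Decline and death will cause loss in both arms. Only the excess loss due to the rule matters, among people who would have replied.
- *The result must favour the intervention.* The article says only that withdrawal may be due to deterioration. It also says the service lasts as long as it is needed, so some may leave because they are doing better.
- *Intention to treat is broken.* Analysis by randomised arm remains possible, and a mixed model, imputation and sensitivity analyses are planned, with detail that may sit in an analysis plan not shown.

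It is also fair that the withdrawal rates are assumed. The protocol's planning figure is 5% total attrition, although the description of the wait-list design expects substantial loss to illness or death.

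None of this removes the core point. Seeking the outcome still depends on a post-randomisation event that differs by arm, the planned analyses cannot see decline after baseline, and the named dropout analysis does not cover the immediate arm.

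**Conclusion.** The concern holds in a conditional form. The rule compromises the intention-to-treat comparison at week 4 and conflicts with the statement that all participants complete that assessment. It can produce arm-dependent informative missingness, with bias towards the intervention if withdrawal reflects deterioration.

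For a given rate and gap, the tabulated figures are an approximate upper bound, because they treat every withdrawer as someone who would have replied and allow no matching informative loss in the wait-list arm. On that footing the bias is small at 5% withdrawal (0.03 to 0.04 SD). At 10% it is material: 0.06 to 0.09 SD, between a quarter and a half of the target effect, with two-sided error of about 13% to 25%. The rate, the gap and the sign all rest on assumptions that the article neither supplies nor rules out.

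**What to change.** Separate withdrawal from the service from withdrawal from data collection.
- Seek the week-4 and later questionnaires in both arms whatever the service use, unless the participant declines, has died, or the site reports that contact is inappropriate or cannot confirm the person's status.
- Apply this one stop-mailing rule in both arms, state how leaving the waiting list is handled, and record the reason for each missing questionnaire by arm.
- Extend the dropout analysis under Comparison between arms to the immediate arm.
- Add a delta-adjusted (missing-not-at-random) sensitivity analysis in which the assumed shortfall for missing outcomes can differ by arm.

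The cost is a short change to the protocol and information sheet, plus some extra status checks and mailings. Status will be unavailable for some people who leave, so some imbalance may remain. The recorded reasons will show how much, and the sensitivity analysis will show whether it matters. The change to data collection must come before follow-up, since a week-4 score not sought at the time cannot be obtained later.
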